## Abstract

**Background:**

More than 6200 End Stage Renal Disease patients in the Netherlands are dependent on dialysis, either performed at home or in a dialysis centre. Visiting a dialysis centre three times a week is considered a large burden by many patients. However, recent data regarding the effects of dialysis at home on quality of life, clinical outcomes, and costs compared with in-centre haemodialysis are lacking.

**Methods:**

The Dutch nOcturnal and hoME dialysis Study To Improve Clinical Outcomes (DOMESTICO) is a nationwide, prospective, observational cohort study that will include adult patients starting with a form of dialysis. Health-related quality of life, as the primary outcome, clinical outcomes and costs, as secondary outcomes, will be measured every 3–6 months in patients on home dialysis, and compared with a control group consisting of in-centre haemodialysis patients. During a 3-year period 800 home dialysis patients (600 peritoneal dialysis and 200 home haemodialysis patients) and a comparison group of 800 in-centre haemodialysis patients will be included from 53 Dutch dialysis centres (covering 96% of Dutch centres) and 1 Belgian dialysis centre (covering 4% of Flemish centres).

**Discussion:**

DOMESTICO will prospectively investigate the effect of home dialysis therapies on health-related quality of life, clinical outcomes and costs, in comparison with in-centre haemodialysis. The findings of this study are expected to ameliorate the shared decision-making process and give more guidance to healthcare professionals, in particular to assess which type of patients may benefit most from home dialysis.

**Trial registration:**

The DOMESTICO study is registered with the National Trial Register on (number: NL6519, date of registration: 22 August 2017) and the Central Committee on Research Involving Human Subjects (CCMO) (number: NL63277.029.17).

**Electronic supplementary material:**

The online version of this article (10.1186/s12882-019-1526-4) contains supplementary material, which is available to authorized users.

## Background

In the Netherlands, over 6200 patients with End Stage Renal Disease (ESRD) are dependent on dialysis, and over the past 15 years, the number of dialysis patients has increased by more than 20% [1–3]. The burden of dialysis is high and the health-related quality of life (HRQoL), which is presently considered to be the most important outcome parameter in dialysis patients, is much worse than that of healthy people [4]. As patient survival is poor, with a median five-year survival rate of only 45%, optimising HRQoL is of great importance for this growing group of patients [5, 6].

Besides its impact on HRQoL, dialysis is also an expensive treatment. In the Netherlands, the estimated costs are approximately 570 million euro per year (639 million US dollars) and are still increasing. [Personal communications, [name], National Institute for Public Health and the Environment, 2019] This makes dialysis by far the highest cost-consuming treatment in internal medicine, not only calculated per individual patient, but also if total treatment costs are taken into account [7].

Home dialysis has a potential positive effect on HRQoL because it offers flexibility to patients and greater freedom [8]. Moreover, home dialysis is possibly a more cost-effective therapy if less nursing staff is needed, when patients perform their treatment autonomously or with help of an informal caregiver. Despite these potential advantages, currently more than 80% of dialysis patients are treated with in-centre haemodialysis (ICHD). Furthermore, the percentage of patients treated with home dialysis is steadily decreasing in the Netherlands, from 32% in 2002 to 18% in 2018. This decline is mainly attributable to a reduction in the number of patients performing peritoneal dialysis (PD), the main home based therapy, with 1519 PD patients (30% of total dialysis patients) in 2002 versus 894 PD patients (14% of total dialysis patients) in 2018 [1].

Available evidence regarding the effects of home dialysis compared with ICHD on HRQoL, a Patient Reported Outcome (PRO), is limited. Most studies have a cross-sectional design and lack adequate correction for confounding among dialysis groups [9–38]. Also, the characteristics of patients starting with some kind of home dialysis treatment have changed remarkably over the past years. Previously, those patients were typically young, working people with little comorbidities, whereas during the last years the general home dialysis population is older and often suffers from multiple comorbidities [2]. This could influence clinical outcomes such as mortality and hospitalisation rate. Finally, there are limited data available regarding the cost-effectiveness of home dialysis.

To investigate the effect of home dialysis on HRQoL, clinical outcomes, and costs, the Dutch nOcturnal and hoME dialysis Study To Improve Clinical Outcomes (DOMESTICO) has been initiated. The aim of this study is to compare HRQoL, clinical outcomes, and cost-effectiveness of home dialysis with ICHD. The hypothesis is that home dialysis is associated with better HRQoL, at least comparable clinical outcomes and lower costs, compared to ICHD.

## Methods

### Study design

DOMESTICO is a nationwide, prospective, observational cohort study comparing home dialysis with ICHD. The maximum follow-up period of the study is 48 months. At present, 53 Dutch dialysis centres (covering 96% of Dutch centres) and 1 Belgian dialysis centre have agreed to recruit patients (Fig. 1). The study is conducted according to the principles of the Declaration of Helsinki and in accordance with the Medical Research Involving Human Subjects Act (WMO).

**Fig. 1 Fig1:**
[figure not shown]
Participating centres. The red dots indicate the participating centres: 53 Dutch dialysis centres (covering 96% of Dutch centres) and 1 Belgian dialysis centre

### Study population

All patients, aged 18 years and older, with ESRD that start with a form of dialysis in the participating centres, between December 2017 and December 2020, are eligible for this study. These patients are allowed to have a history of renal replacement therapy (RRT), however they have to (re) start dialysis during the study period for example due to kidney transplant failure (with or without previous dialysis). All these patients are defined as ‘incident patients’. Prevalent dialysis patients, and patients with a life expectancy shorter than 3 months or an expected kidney transplantation within 3 months, are excluded. Patients have to provide written informed consent before participating in the study.

### Inclusion

Patients are included in the period within four weeks before to four weeks after start of dialysis. If patients are missed for inclusion within this timeframe (for example, due to acute start of dialysis), they can be included at 3 months (± 2 weeks) after start of dialysis. Start of dialysis is defined as the first PD session performed at (a nursing) home (excluding PD-training) or, in case of ICHD, the first haemodialysis session performed in a centre (excluding continuous RRT).

The first patient was included in December 2017 and the study has currently started in 45 centres with 338 participating patients (Fig. 2).

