#### Secondary outcome parameters

Secondary outcome parameters are hospitalisation, mortality, other clinical parameters, costs, and technique failure.

The cause of each hospitalisation episode will be categorised into the following categories (using ICD-10 codes) [47]:
Cardiac (including myocardial ischaemia/infarction, cardiac arrest/arrhythmia, cardiac failure, fluid overload/pulmonary edema, haemorrhagic pericarditis);Vascular disease (including pulmonary embolus, stroke, cerebrovascular haemorrhage, ruptured vascular aneurysm, mesenteric infarction, peripheral arterial disease);Infection, non-dialysis related (including bacteraemia/sepsis, cardiac infection, HIV, osteomyelitis, respiratory infection, urinary tract infection);Dialysis related (including dialysis access infection, peritonitis, PD catheter leakage/exchange/removal, fistula operation, renal fluid overload, bleeding);Malignancy;Bleeding, non-dialysis related (including intracranial bleeding, gastro-intestinal bleeding, other causes of bleeding);Other causes.

Mortality will be categorised into the following categories (using ERA-EDTA codes) [48]:
Sudden death ‘with unknown cause’;Cardiac (including myocardial ischaemia/infarction, cardiac arrest/arrhythmia, cardiac failure, fluid overload/pulmonary edema, haemorrhagic pericarditis);Vascular (including pulmonary embolus, stroke, cerebrovascular haemorrhage, ruptured vascular aneurysm, mesenteric infarction, peripheral arterial disease);Infectious, dialysis related (including dialysis access infection, peritonitis);Infectious, non-dialysis related (including bacteraemia/sepsis, cardiac infection, HIV, osteomyelitis, respiratory infection, urinary tract infection);Malignancy;Bleeding (including dialysis related bleeding, intracranial bleeding, gastro-intestinal bleeding, other causes of bleeding);Overall deterioration in clinical condition/stopping dialysis;Other causes.

Besides hospitalisation and mortality, several clinical parameters will be recorded including blood pressure and use of antihypertensive drugs, haemoglobin and use of erythropoiesis-stimulating agents, phosphate levels and use of phosphate binders, vascular access parameters, and nutritional status.

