*SF-12* Short Form-12, *DSI* Dialysis Symptom Index, *iPCQ* Institute for Medical Technology Assessment (iMTA) Productivity Cost Questionnaire, *iMCQ* iMTA Medical Cost Questionnaire, *SeMaS* self-management screening questionnaire

Finally, technique failure rate of home dialysis, defined by a composite outcome of death or transfer to ICHD, will be assessed. Both a 30-days and a 180-days definition of technique failure will be used according to the minimum number of days the patient received ICHD after cessation of home dialysis [56]. Permanent technique failure is defined by death or transfer to ICHD (using the 180-days definition), or cessation of dialysis. Death-censored technique failure will be reported separately. Transfer to kidney transplantation is not considered to be technique failure and will also be reported separately [56].

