### Sample size calculation

For the primary outcome HRQoL, obtained with the SF-12, a sample size of 350 patients is required. To obtain a clinically relevant difference between groups of 3 points in the SF-12 summary scores, after a median of 12 months follow-up, 175 patients per group are needed (assumed standard deviation = 10 points, α = 0.05, β = 0.20) [46, 57–59].

However, for the EQ5D-5L, an important component for the secondary outcome cost-effectiveness, a sample size of 1400 patients (700 patients per group) is needed. A difference of 0.03–0.07 points between groups after a mean follow-up of 12 months is considered clinically relevant [44, 60, 61]. The standard deviation in dialysis groups ranges from 0.1 to 0.22 [62, 63]. Assuming a common standard deviation of 0.20 and the lowest, still clinically relevant score, a total of 1400 patients (700 patients per group) will be sufficient to detect a difference of 0.03 points in the EQ5D-5L score between groups (α = 0.05, β = 0.20).

When approximately 10% loss to follow up is taken into account, a group of 800 home dialysis patients and a comparison group of 800 ICHD patients has to be included in order to have sufficient power to analyse both outcomes. Since the ratio between PD patients and home haemodialysis (HHD) patients in the Netherlands is expected to be 3:1 in future years, the home dialysis group will consist of 600 PD and 200 HHD patients.

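### Start of dialysis falls after training for PD, at the first in-centre session for ICHD, and is undefined for HHD, so the compared groups lack a common time origin

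*Protocol article*

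**What the plan says.** All of the following is in the protocol article.

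- **Inclusion, PD rule:** "Start of dialysis is defined as the first PD session performed at (a nursing) home (excluding PD-training", which places training before the start.
- **Inclusion, ICHD rule:** "in case of ICHD, the first haemodialysis session performed in a centre (excluding continuous RRT", so the clock starts with in-centre treatment itself.
- **HHD:** Inclusion gives no rule, yet under Sample size calculation "the home dialysis group will consist of 600 PD and 200 HHD patients".
- **Windows, all modalities:** "Patients are included in the period within four weeks before to four weeks after start of dialysis". Patients missed then have a second chance: "they can be included at 3 months (± 2 weeks) after start of dialysis". The example given for missing the first window is an acute start.
- **Study population:** "Prevalent dialysis patients, and patients with a life expectancy shorter than 3 months or an expected kidney transplantation within 3 months, are excluded". No cut-off separates a prevalent patient from an incident one who has had some in-centre sessions before going home.
- **Outcomes that depend on a clock:** "Secondary outcome parameters are hospitalisation, mortality, other clinical parameters, costs, and technique failure". Technique failure applies to the home group only: "technique failure rate of home dialysis, defined by a composite outcome of death or transfer to ICHD, will be assessed".

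Statistical analysis plans Kaplan-Meier curves for hospitalisation, mortality and technique failure, and repeated-measures models where measurements recur. It names no time origin other than the start defined under Inclusion.

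**The concern.** The comparison of home dialysis with ICHD needs both groups to be followed from an equivalent moment. Here a PD patient must get through training, and any in-centre bridging, to reach the defined start. An ICHD patient who dies or is admitted in the equivalent early weeks has already started.

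Three things are at stake:

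1. **Selection at entry.** Early deaths and early failures on the way to home PD may never be counted in the home group.
2. **Unequal time on dialysis.** If the 3-, 6- and 12-month questionnaires are timed from this start, home patients have been treated longer at each comparison, including that of the primary outcome.
3. **Ambiguous membership.** A patient treated in-centre before PD or HHD could be classed as home, as ICHD, or as prevalent and so excluded.

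The listed confounders describe who chooses home dialysis. Adjusting for them does not repair a time zero that differs by group.

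**Working it through.** **1. The plan's own figures.** With two-sided α = 0.05 and 80% power, n per group = 2 × (1.960 + 0.842)² × SD² / Δ².
- SF-12: SD 10, Δ 3 gives 175 (stated 175).
- EQ-5D-5L: SD 0.20, Δ 0.03 gives 698 (stated 700).
- Allowing 10% loss: 700 / 0.9 = 778 (stated 800).

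All reproduce, and none depends on day 0. The sample size is unaffected.

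**2. The rules side by side.**

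| Modality | Planned n | Day 0 | Left before day 0 |
|---|---|---|---|
| PD | 600 | first session at home or nursing home | training, any in-centre bridging |
| HHD | 200 | not stated | unknown |
| ICHD | 800 | first in-centre session | continuous RRT |

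HHD is 200/800 = 25% of the home group and 200/1600 = 12.5% of the cohort.

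**3. How many PD patients could be missed (illustration only).** Training length is not given; I assume w = 2 to 12 weeks. The Background's 45% five-year survival gives a constant hazard h = −ln(0.45)/5 = 0.160 per year. The proportion dying in w weeks is 1 − exp(−h × w/52). The last two columns show w as a percentage of 13 and 52 weeks, that is, the extra time since first treatment at the 3- and 12-month visits. They assume that visits run from the defined start and that training involves dialysis.

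| w (weeks) | Dying | Per 600 PD | Extra time at 3 months | Extra time at 12 months |
|---|---|---|---|---|
| 2 | 0.6% | 3.7 | 15% | 4% |
| 4 | 1.2% | 7.3 | 31% | 8% |
| 8 | 2.4% | 14.6 | 62% | 15% |
| 12 | 3.6% | 21.7 | 92% | 23% |

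**4. Does that measure bias?** No. Under a constant hazard, 12-month mortality among those alive at a later origin is still 1 − exp(−0.160) = 14.8%. Moving the origin changes the result only if risk in the early weeks differs from later risk, or if those who fail in training differ from those who complete it. The documents give no figure for either.

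**5. The opposite direction.** Suppose 10%, 30% or 50% (assumed) of 800 ICHD patients enter late, at about 13 weeks. Unobserved early deaths are 800 × share × (1 − exp(−0.160 × 13/52)), or about 3, 9 and 16. Late entry for PD is counted from the later PD start, so a late PD entrant has survived training plus about three months.

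**The case against.** The strongest reply is that the definition stands under Inclusion and anchors the recruitment window. A condensed article may leave the analysis origin to the full plan. This stands in part: the article does not say that events are counted from this start, so the consequences above are conditional. But it is a stated rule that differs by modality, no other origin is named, and the HHD rule is absent from that same definition.

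Four stronger readings are tempting, and the documents do not support them.

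- **A reader might infer that early events are lost from the home group only.** Late entry at 3 months is open to every modality and can hide early ICHD events. Continuous RRT before the first ICHD session is also left out.
- **A reader might call PD training immortal time.** That term applies when event-free waiting time is credited to a group. Here the time precedes the start and is credited to nobody; the problem is selection, or left truncation. Immortal time would arise only if in-centre weeks before home treatment were credited to home.
- **A reader might divide 0.6–3.6% by 14.8% and conclude that home mortality is understated by 4–25%.** Step 4 of the working shows that no bias follows under that constant hazard.
- **A reader might infer that training costs and admissions are dropped.** The counting date is not given. Inclusion may precede the start by four weeks, costs come from the chart over the study, and services such as home dialysis are added to the cost questionnaire.

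Technique failure has no ICHD counterpart, so the issue there is under-counting of early failures.

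**Conclusion.** The point holds as a time-zero misalignment with selection at entry. Day 0 follows training for PD, coincides with the first in-centre session for ICHD, and is missing for a quarter of the planned home group.

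If follow-up runs from this start, the effect probably favours PD for early mortality, admissions and technique failure. Late entry of ICHD patients may partly offset it. For HHD the direction is unknown because the rule is missing. For HRQoL it is unknown because nothing shows which way a few weeks' shift moves the scores. A claim that every hypothesis is tilted towards home dialysis would therefore go too far.

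The size cannot be computed. The range of about 4 to 22 deaths per 600 PD patients rests on an assumed 2 to 12 weeks of training and a constant five-year average hazard. The eligibility rule excludes patients with a short life expectancy, so early risk may differ from that average.

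**What to change.** 1. Add an explicit start of dialysis for HHD, and say how patients treated in-centre before going home are classified, including when they count as prevalent.
2. For every patient, record two dates: the first dialysis session of any kind (training and bridging included, continuous RRT excluded) and the first home session.
3. Use the first session as the common analysis origin, with delayed entry at the inclusion date for all modalities, including the 3-month entrants. The consent windows can then stay. Delayed entry is essential: after 12 weeks of training and a further 4 weeks to inclusion, a patient would join 16 weeks after the new origin, and those weeks must not count as time at risk.
4. Group by the modality intended at inclusion, with modality as a time-varying exposure in a supportive analysis.
5. State that training-period admissions and costs count to the home group.

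The cost is a change of wording and a little more abstraction from charts already in use. The home-group result may look less favourable. Delayed entry does not recover patients who die in training before consent, so that limitation should be reported. At submission 338 of 1600 patients (21%) had been included, so most dates can still be collected prospectively.

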Direct healthcare costs, patient costs, and costs with regard to productivity losses will be assessed with a subset of questions from the Institute for Medical Technology Assessment (iMTA) Productivity Cost Questionnaire (iPCQ) and the iMTA Medical Cost Questionnaire (iMCQ) [49, 50]. To capture all health care costs for the population under research a small number of disease specific services are added to the standard iMCQ, e.g. home dialysis. Given the fact that many patients need substantial help from close relatives, also use of informal care by patients will be assessed. The costs related to the healthcare consumption, the dialysis procedures, the diagnostic tests and (over-the-counter) medication will be derived from the patient’s medical chart during the study. Unit costs will be derived from the Dutch manual for costing studies [51].

To further examine cost-effectiveness, the EuroQol-5D-5L (EQ5D-5L) questionnaire will be used. The EQ-5D-5L measures HRQoL on the following 5 domains: mobility, self-care, usual activities, pain/discomfort, and anxiety/depression. Each domain has 5 levels of functioning, ranging from ‘no problems’ to ‘extreme problems’. The EQ-5D-5L also contains a visual analogue scale on which the current health state can be indicated. The EQ-5D scores can be used to calculate utilities, which describe HRQoL on a scale from 0 (dead) to 1 (perfect health). Utilities can be combined with survival to calculate quality adjusted life years (QALYs). As outcome measure for cost-effectiveness, the costs per additional QALY will be analysed [52, 53].

All participating patients will also receive a self-management screening questionnaire (SeMaS) at baseline, in order to investigate whether self-management can predict a successful home dialysis treatment. This questionnaire shows the abilities and possible barriers for self-management by asking questions about the burden of disease, locus of control, self-efficacy, social support, coping style, anxiety, depression, and skills [54, 55].

Table 2 provides an overview of the moments when participating patients will fill in the aforementioned questionnaires.

**Table 2 Tab2:** Overview questionnaires

Visit	SF-12 and DSI	iPCQ and iMCQ	EQ-5D-5L	SeMaS
Baseline	X	X	X	X
At 3 and 6 months	X	X	X	
At 9 months and every 6 months thereafter		X		
At 12 months and every 6 months thereafter	X	X	X	

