### Statistical analysis

All statistical analyses will be performed using statistical software such as SPSS and Stata. Univariable and multivariable regression analysis will be conducted. In case of repeated measures, multilevel analysis or generalised estimating equations will be applied. Possible confounders determined a priori are age, gender, marital status, level of education, work status, cause of renal failure, prior RRT with dialysis vintage, comorbidities, albumin, body mass index, and protein energy wasting. Cumulative incidence of hospitalisation, mortality, and technique failure will be reported in Kaplan Meier curves. In case of missing data, multiple imputation techniques will be used to impute the missing values where appropriate.

Overall costs will be compared across the treatment groups and 95% confidence intervals will be estimated using bootstrapping techniques. The cost-effectiveness of different dialysis modalities will be determined using a state transition model. This model captures the changes in treatment modality, including transplantation, over time. The results of the DOMESTICO study will be used as input parameters for this model.

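### Living situation before dialysis is not among the prespecified confounders, although nursing-home PD counts as home dialysis and nursing-home residents may be in either group

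*Protocol article*

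**What the plan says.** **Who is in the home group.** Under Inclusion, the article fixes the start date for PD: "Start of dialysis is defined as the first PD session performed at (a nursing) home (excluding PD-training"). A first session in a nursing home therefore qualifies. Under Sample size calculation, "the home dialysis group will consist of 600 PD and 200 HHD patients", so no PD patient falls outside the home group. The exclusions under Study population concern prevalent dialysis, short life expectancy and imminent transplantation. None concerns residence, so nursing-home residents may enter the in-centre haemodialysis (ICHD) group as well.

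**What is adjusted for.** Under Statistical analysis: "Possible confounders determined a priori are age, gender, marital status, level of education, work status, cause of renal failure, prior RRT with dialysis vintage", followed by "comorbidities, albumin, body mass index, and protein energy wasting". Nothing in the list records residence, living alone or with others, or functional dependency.

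**Costs.** "Overall costs will be compared across the treatment groups and 95% confidence intervals will be estimated using bootstrapping techniques". That sentence names no covariates.

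**Related data.** Under Secondary outcome parameters, "also use of informal care by patients will be assessed", as part of the costing. The baseline self-management questionnaire (SeMaS) asks about social support, for the purpose of predicting successful home treatment. Neither is named as an adjustment variable.

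**The concern.** The design is non-randomised by choice. The Discussion relies on measured covariates to deal with confounding by indication, and the Background faults earlier studies for inadequate correction. The stated list therefore carries much of the weight of the comparison.

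Where a patient lives before dialysis precedes the choice of modality and can shape it, through space and available help. It can also affect quality of life, admissions, death and use of care by routes that have nothing to do with modality. That is the structure of a confounder.

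Marital status is the nearest item on the list, but it is a weak stand-in. A widowed patient living with family and a widowed patient in a nursing home have the same value. Age and comorbidities capture dependency only in part.

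If the groups differ in who lives where, part of that difference could appear as an effect of modality. Costs look most exposed, because formal and informal care both depend on living situation.

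**Working it through.** **1. The plan's own figures.** With two-sided α = 0.05 and 80% power, n per group = 2(1.960 + 0.842)² × SD²/Δ².

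- SF-12 (Δ = 3, SD = 10): 2 × 7.849 × 100/9 = 174.4, so 175. This matches the stated 175.
- EQ-5D-5L (Δ = 0.03, SD = 0.20): 2 × 7.849 × 0.04/0.0009 = 697.7, so 698. The plan rounds to 700.
- Loss of 10%: 700/0.9 = 778, and 800 are planned.

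The sample sizes hold, and nothing below changes them.

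**2. Bias formula.** Bias = (difference between groups in the share of nursing-home residents) × (outcome gap between residents and others that remains after the listed covariates).

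The document gives neither input, so both are assumptions: an imbalance of 2, 5 or 10 percentage points, an EQ-5D gap of 0.1 to 0.3 and an SF-12 gap of 5 to 10 points.

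| Imbalance | EQ-5D bias, gap 0.1 / 0.2 / 0.3 | Share of 0.03 target | SF-12 bias, gap 5 / 10 | Share of 3-point target |
|---|---|---|---|---|
| 2 points | 0.002 / 0.004 / 0.006 | 7% / 13% / 20% | 0.1 / 0.2 | 3% / 7% |
| 5 points | 0.005 / 0.010 / 0.015 | 17% / 33% / 50% | 0.25 / 0.5 | 8% / 17% |
| 10 points | 0.010 / 0.020 / 0.030 | 33% / 67% / 100% | 0.5 / 1.0 | 17% / 33% |

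**3. Effect on the test.** At 700 per group, the standard error of the EQ-5D difference is 0.20 × √(2/700) = 0.0107. With no true effect, the chance of a significant result is 1 − Φ(1.96 − b/0.0107) + Φ(−1.96 − b/0.0107):

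- b = 0.002: 5.4%
- b = 0.005: 7.5%
- b = 0.010: 15%
- b = 0.015: 29%
- b = 0.020: 46%
- b = 0.030: 80%

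**4. How strong the assumptions are.** Against the plan's SDs, an EQ-5D gap of 0.1 is 0.1/0.20 = 0.5 SD, and 0.3 is 1.5 SD. An SF-12 gap of 5 to 10 points is 0.5 to 1.0 SD. A gap of 1 SD or more that survives adjustment for age, comorbidities, albumin, protein energy wasting and work status is large. The upper rows and columns are outer bounds rather than expectations.

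**5. Direction.** The formula is signed. More residents in the home group would pull its scores down, and more in the ICHD group would do the reverse. The same arithmetic applies to living alone. If fewer home patients live alone, that part could favour home dialysis. No sign follows from the text.

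**The case against.** **The list is of possible confounders in a condensed article.** The final covariate set may sit in a fuller document, and almost any observational list invites one more covariate. This has some force. But the article does not leave the matter open: it prints a list and says that it was fixed in advance. Residence is also not an arbitrary addition, because the article itself writes nursing homes into its definition of the start of PD.

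**Related data are collected.** Informal care and social support cover part of who has help. That is true, and it narrows the gap. Neither is named for adjustment, and neither is described as recording residence. The case report form is not shown, so residence may already be captured. In that case only the analysis needs to change.

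**A nursing home is the resident's home.** A reader might infer that pooling nursing-home PD with other home dialysis is a mistake, since the Background expects lower costs "when patients perform their treatment autonomously or with help of an informal caregiver". The document does not support that inference. The sentence offers a possible mechanism, conditional on needing fewer nursing staff, and does not define the exposure. The contrast under study is home against in-centre, and the Background cites an older, more multimorbid home population. Including these patients is a legitimate definition.

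**The size is assumed throughout.** This stands. At the low end the bias is 0.002 and the rejection rate 5.4%, which is close to nominal.

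**Conclusion.** The point holds as possible residual confounding from a variable that the stated list leaves out. It is a worthwhile improvement and not a demonstrated bias.

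A reader might take from the table that the false-positive rate will be 15% to 29%, or that lower dependency and lower care costs will be credited to home dialysis. The document supports neither. The 15% and 29% figures need a 5-point imbalance together with EQ-5D gaps of 0.2 and 0.3 that remain after adjustment, and no share, imbalance or gap is reported. The sign is unknown because residents may be in both groups.

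What can be said is conditional. Over the assumed ranges, the bias runs from negligible to as large as the EQ-5D target, and up to a third of the SF-12 target. No cost figure can be given, since the article reports no unit costs or care use by residence. Costs are singled out because of how directly they depend on living situation, and because the sentence describing that comparison states no adjustment.

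**What to change.** 1. Under Statistical analysis, add living situation just before the start of dialysis (own home alone, own home with others, nursing home) to the prespecified confounders. Use it in both groups, and for the cost comparison as well as for quality of life.
2. Word the item so that it refers to the time before the first session, including for patients who enter by the 3-month route. A later move may be a consequence of treatment and should not be adjusted away.
3. Add one sensitivity analysis that repeats the quality-of-life and cost comparisons without nursing-home residents in either group. If residents are few, it will change little and will show that the question is closed.

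The definition of home dialysis and the sample size stay as they are.

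**Cost.** One baseline item, if the case report form does not already hold it, one covariate and one extra analysis. The downside is back-filling for patients already enrolled: 338 of 1600 at submission, or 21%. Values that cannot be recovered can go through the multiple imputation already planned.
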